### Statistical analysis

We will describe the distribution and group differences of the subjects’ general characteristics and the incidence of HPV infection and relevant disease in each age cohort by the exposure status. The categorical data will be described by frequency (proportion) and the Chi-squared test will be performed to show the group difference. The continuous data will be described by mean (standard deviation), and non-normal distribution continuous data will be described by median (quantiles), and then the ANOVA or Wilcoxon rank-sum test will be performed to compare the difference across age groups. Also, the Kaplan–Meier method will be used to draw the survival graph, based on the actual number of cases of each endpoint.

The Logistic Regression will be performed to analyze the impact on HPV 16/18 infection, and HPV 31/33/45 infection in each birth cohort 3 years after vaccination, after adjusting the confounders such as the demographic characteristics, history of sexual behavior, personal behavior history, etc. The vaccine impact will be calculated by using (1-Relative Risk) and its 95% CI.

Stratification analysis will be conducted by frequency of sexual activity, numbers of sexual partners, extramarital sexual activity, family annual income, education level, and cervical cancer screen history. The interaction term between the above factors and HPV vaccination will be introduced into the Logistic regression model, and the differences between the model with interaction term and the model without interaction term will be compared, so as to evaluate the interaction between different factors and HPV vaccination.

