## Abstract

**Background:**

Cervical cancer is one of the most common cancers in women and could be prevented by human papilloma virus (HPV) vaccination. *Cervarix*, the first available HPV vaccine, has been widely administrated to Chinese women, while little was known about its effect on the prevention and control for HPV related diseases in China. The study aims to assess the impact of *Cervarix* on HPV infection and cervical related diseases in real world.

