**Discussion:**

This prospective cohort study will assess the impact of HPV vaccine on HPV infection and related cervical diseases in women aged 9–45 years, which makes up for the lack of evidence in Chinese women. The results of this study will provide support for understanding the impact of HPV vaccination in China, and make a contribution to increasing HPV vaccination and cervical cancer screening coverage in China.

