### Aims

The study aims to evaluate the impact of the AS04 adjuvanted HPV 16/18 vaccine (Brand name: *Cervarix),* for HPV infection and related cervical diseases in real world, with the following objectives:To describe the incidence of HPV 16/18 infection by exposure status, and to evaluate the effectiveness of *Cervarix* on HPV 16/18 infection in birth cohortsTo describe the incidence of cervical lesions or diseases, and other 12 high-risk HPV infection by exposure status in birth cohorts

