#### Secondary endpoints

Cervical infection with HPV-16 and/or HPV-18 over 12 months (measured by two tests with an interval of 12 months), *defined as at least one positive HPV-16 or HPV-18 DNA PCR assay at the additional visit in 12 months after getting the positive HPV-16 or HPV-18 test result at enrollment (Month 0) or follow-up (Month 36) or any additional screenings during the study period.*

Cervical infection with 12 other high-risk HPV besides of type 16/18 (by PCR), *defined as at least one positive for HPV 31/33/35/39/45/51/52/56/58/59/66/68 or multiple types DNA PCR assay at enrollment (Month 0) or follow-up (Month 36) or any additional screenings during the study period.*

Any cervical lesions or diseases in birth cohorts, *defined as atypical squamous cells of undefined significance (ASC-US), atypical glandular cells (AGC), atypical squamous cells, cannot exclude for highly squamous intraepithelial lesions (ASC-H), low-grade squamous intraepithelial lesion (LSIL), high-grade squamous intraepithelial lesion (HSIL), Cervical Intraepithelial Neoplasia (CIN) 1, CIN2, CIN3, squamous cell carcinoma (SCC), adenocarcinoma *in situ* (AIS) and adenocarcinoma (ADC). Any hr-HPV type infection is defined as at least one positive for HPV 16/18/31/33/35/39/45/51/52/56/58/59/66/68 or multiple types DNA PCR assay in the aforesaid cervical sample.*

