**Fig. 2 Fig2:**
[figure not shown]
Study procedure

Subjects will be stratified into three age groups (9–20 y/o, 21–30 y/o and 31–45 y/o) and divided into exposed and non-exposed groups by vaccination status. The exposed group will include subjects who received 1 or 2 doses of *Cervarix* and the non-exposed group will include subjects who did not receive any doses of HPV vaccine.

During the study period, two visits will be scheduled for all subjects at Month 0 and Month 36, which means the follow-up period will be 3 years. In the first visit, the questionnaire survey will be administrated for all the subjects to obtain the demographic information, sexual history, menstrual and obstetrical histories, etc. For the ones who are eligible for the cervical cancer screening (i, Have sexual debut at the enrollment; ii, no contradiction of screening and iii, are willing to undergo the screening), the type-specific HPV DNA PCR testing will be given within 2 weeks after the enrollment. After 3-years follow-up, the subjects will be called back for the second visit. A questionnaire which measures any changes of behavior during the follow-up period will be performed. Then the second screening with type-specific HPV DNA PCR testing will be given within 2 weeks after the call-back.

At each visit, type-specific HPV DNA PCR testing will be the primary screening approach, and for the ones with unsatisfactory findings (i.e., hr-HPV infection) will be referred to the local abnormal cervical cancer screening results management system for further medical activities (Fig. 1)

By the end of the follow-up period, the prevalence of the HPV infection, cervical disease (e.g., CIN1, CIN2, CIN3, SCC, AIS, etc.) will be described in each birth cohort by their exposure status. If the sample size is sufficient, the effectiveness of *Cervarix* will be assessed as the exploratory objective.

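### The aim claims impact on cervical disease, but disease is only described and tested without adjustment; the confounder-adjusted model names infection outcomes only

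*Protocol article*

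**What the plan says.** **The aim covers disease.** The Abstract's Background states: "The study aims to assess the impact of *Cervarix* on HPV infection and cervical related diseases in real world". The Abstract's Discussion repeats it: "This prospective cohort study will assess the impact of HPV vaccine on HPV infection and related cervical diseases in women aged 9–45 years". The lead sentence of Aims says the vaccine's impact will be evaluated "for HPV infection and related cervical diseases in real world". The closing paragraph of Feasibility and limitation makes the same claim. Disease is also a named secondary endpoint, "Any cervical lesions or diseases in birth cohorts", running from ASC-US to invasive cancer.

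**The objectives are narrower.** Objective 1 in Aims attaches effectiveness to HPV 16/18 infection. Objective 2 only describes the incidence of lesions and of the other high-risk types. Study procedure agrees: infection and disease "will be described in each birth cohort by their exposure status". It then adds: "If the sample size is sufficient, the effectiveness of *Cervarix* will be assessed as the exploratory objective", without naming the outcome.

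**The analysis.** Statistical analysis places disease in the descriptive comparison by exposure within each age cohort. For categorical data there, "the Chi-squared test will be performed to show the group difference". Kaplan–Meier graphs are planned for each endpoint. The adjusted model is set out separately: "The Logistic Regression will be performed to analyze the impact on HPV 16/18 infection, and HPV 31/33/45 infection in each birth cohort", with adjustment for demographics, sexual history and personal behaviour. The effect measure, one minus the relative risk with a 95% CI, follows directly on that model.

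**The concern.** The groups are not randomised. Background says that recipients paid for the vaccines themselves. Exclusion criteria remove from the non-exposed group women who clearly intend to be vaccinated within three years. Vaccinated and unvaccinated women can therefore differ in income, education, sexual behaviour and use of screening.

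The plan accepts this for infection and adjusts for it. Background describes HPV infection as the main cause of cervical cancer, so the same factors bear on lesions. Screening habits matter further, because a lesion is recorded only in a woman who is screened.

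Followed as written, the study would report adjusted results for infection next to a crude p-value for disease, under an aim that speaks of impact on both. A significant crude difference could then be taken as a vaccine effect, and a null one as absence of effect, when either may reflect who chose vaccination.

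**Working it through.** **1. The plan's own figures, and whether they concern disease.** Table 1 takes a 0.02 incidence of HPV 16/18 infection, effectiveness of 0.83, 0.66 and 0.50, α = 0.05, power 0.80 and a 1:1 ratio. The two-sided pooled formula is

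n per group = [z(0.975)·√(2p̄(1−p̄)) + z(0.80)·√(p₁(1−p₁) + p₂(1−p₂))]² / (p₁−p₂)², with p₁ = 0.02 and p₂ = 0.02 × (1 − effectiveness).

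| Age group | p₂ | n computed | n stated | Analysis total / 0.7 | Target stated |
|---|---|---|---|---|---|
| 9–20 | 0.0034 | 658 | 661 | 1889 | 1890 |
| 21–30 | 0.0068 | 1190 | 1208 | 3452 | 3452 |
| 31–45 | 0.0100 | 2319 | 2371 | 6775 | 6776 |

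The stated sizes reproduce to within 2.2%. They all concern HPV 16/18 infection. The article gives no disease rate, effect or power.

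**2. Which planned analyses reach disease.**

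| Analysis in the Statistical analysis section | Reaches disease? | Adjusted? |
|---|---|---|
| Incidence by exposure within age cohort, chi-squared test | Yes | No, apart from the age band |
| Kaplan–Meier graphs for each endpoint | Yes, by implication | No, and no test is named |
| Logistic regression, one minus relative risk | Not named; HPV 16/18 and 31/33/45 infection only | Yes |
| Stratified analysis | No outcome named | By stratum only |
| Interaction terms | Enter the logistic model above | As in that model |

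**3. What the age bands remove.** Comparison within a band controls age in part. Background reports infection peaks below 25 and at 41–45, and free screening from 35. The cut at 25 lies inside the 21–30 band. The later peak and the start of free screening both lie inside the 31–45 band. Age and age-driven detection can therefore still differ between groups within a band.

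**4. Illustration of possible size (assumed inputs, none from the documents).** Suppose the vaccine has no effect on disease and one binary confounder multiplies disease risk by R, with prevalence a in the exposed and b in the non-exposed. Then

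crude RR = [1 + a(R−1)] / [1 + b(R−1)].

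- R = 1.5, a = 0.2, b = 0.3: 1.10 / 1.15 = 0.96, an apparent effectiveness of 4%.
- R = 3, a = 0.2, b = 0.4: 1.40 / 1.80 = 0.78, an apparent effectiveness of 22%.
- R = 1.5, a = 0.3, b = 0.2: 1.15 / 1.10 = 1.05, an apparent effectiveness of −5%.
- R = 3, a = 0.4, b = 0.2: 1.80 / 1.40 = 1.29, an apparent effectiveness of −29%.

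**5. What that would do to the test.** Take 2371 women per group (the 31–45 analysis size) and an assumed disease risk of 0.5% to 5% in the non-exposed. With a crude RR of 0.78 and no true effect, the chance of a significant result favouring the vaccine is 8% to 46%, against a nominal 2.5% in that direction. With a crude RR of 0.92 (R = 2, a = 0.2, b = 0.3: 1.20 / 1.30), it is 4% to 9%.

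**The case against.** The strongest reply is that the analysis matches the objectives. The lead sentence of Aims is spelled out by two objectives, and the one on disease is descriptive. Study procedure says the same. The effectiveness estimate belongs to the infection model, and the chi-squared sentence is a generic one that also serves baseline characteristics. Women with high-risk HPV or cervical abnormality at baseline are excluded and follow-up is three years, so lesions may be few and a descriptive treatment is defensible. A condensed article may also leave models for secondary endpoints to a fuller document.

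Much of this stands. A reader might infer that the plan promises an effectiveness estimate for disease and then performs it badly. It does not: no such estimate is planned, and a crude table is consistent with Objective 2. Nor is the chi-squared test the only between-group display of disease, since Kaplan–Meier graphs are planned as well.

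Two things remain. First, the impact aim appears in four places and is broader than the objective and the analysis beneath it. Second, the article does not merely leave the adjusted model open: it lists that model's outcomes, and disease is not among them, while a significance test between self-selected groups is applied to disease. Strengths of the study mentions adjusting for age in a multi-factor analysis, but the only such analysis specified does not name disease.

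**Conclusion.** The point holds as a mismatch between the aim and the analysis. The article claims to assess impact on cervical disease, describes disease by exposure status, and tests it only without adjustment within broad age bands. The resulting comparison is open to confounding.

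A reader might go further and conclude that the disease result is confounded by a known amount. The documents do not support that. They give no covariate distribution by exposure group, no disease rate and no confounder–disease association, so neither size nor direction can be determined. The crude risk ratios of 0.78 to 1.29 under no vaccine effect rest entirely on the assumed confounder strength and prevalences, and show only what modest imbalance could do.

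The matter concerns a secondary endpoint and leaves the primary HPV 16/18 analysis untouched. It is worth correcting because it decides whether anything about vaccine impact on disease can be concluded.

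**What to change.** Choose one of two courses.

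1. **Keep the impact aim for disease.** Add the secondary lesion or disease endpoint to the outcomes of the confounder-adjusted model, using covariates the questionnaire and health platform already supply, with age as a covariate within the band. If events are few, use a reduced covariate set fixed in advance, or pool the three cohorts with age in the model. The cost is one further model on existing data. The drawback is wide intervals when events are sparse, and unmeasured differences would remain.

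2. **Keep disease descriptive.** Drop the significance test for disease and report counts and incidence by exposure status and age cohort. Reword the Abstract (Background and Discussion), the lead sentence of Aims and the closing paragraph of Feasibility and limitation, so that disease is described with no claim of impact. The cost is a few sentences.

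Under either course, label the Kaplan–Meier graphs for disease as unadjusted.

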## Background

Cervical cancer was the fourth most common cancer in women, with approximately 0.60 million cases and over 0.34 million deaths from cervical cancer worldwide in 2020 [1]. China is one of the countries with the most cases contributed with approximately 0.11 million cases and 0.05 million deaths [2]. Further, both the incidence of cervical cancer and disease burden still increased in the last decades, and its onset age becomes much younger in Chinese women [3, 4]. Human Papillomavirus (HPV) infection is the primary cause of cervical cancer [5], specifically, HPV16 and 18 infections accounted for 84.5% of invasive cervical cancer in China [6].

Expanding the coverage of HPV vaccines is an essential part of the 90–70-90 target proposed by the World Health Organization (WHO) for eliminating cervical cancer [7]. In a modeling study, with 70% coverage of bivalent vaccine, cancer cases can decrease by 58% to 33% in rural areas and 69% to 32% in urban areas at ages of 12 to 55, respectively [8]. China has also been making effort to increase vaccination coverage. Since 2016, HPV vaccines have been introduced for females aged 9–45 in mainland China, such as *Cervarix* (9–45 years old) in 2016, *Gardasil 4* (20–45 years old) in 2017, *Gardasil 9* (16–26 years old) in 2018 and the domestic bivalent HPV vaccine *Cecolin* (9–45 years old) in 2019 [9–12]. These vaccines were not included in the programmed immunization and were paid for by the receivers. Since 2020, some of cities in China have launched free HPV vaccination programs for girls under 14 years, which only included the domestic bivalent HPV vaccine *Cecolin* for now [13, 14]. In addition, China is also popularizing cervical cancer screening to accelerate the elimination of cervical cancer. China has initiated *the Two Cancers (the cervical cancer and breast cancer)* Screening Program in 2009, which provided females aged 35 years and over with cervical cancer and breast cancer screening for free [15]. Screening strategies varied across regions, including HPV-initiated and TCT-initiated tests. As for Yinzhou, Ningbo, where our study will be conducted, the standard cervical cancer screening process initiate with a type-specific HPV DNA PCR testing, and for the ones with HPV infection will be referred to colposcopy or cytology test, while those who are tested negative will be invited for another screening after 3 years (Fig. 1).

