### Exclusion criteria

The following criteria should be checked at the time of study entry. If any apply, the subjects must not be included in the study:Pregnancy at the enrollment.Females with historical cervical diseases (i.e., cervical intraepithelial neoplasia (CIN)1, CIN2, CIN3, and cervical cancer) before the recruitment.After hysterectomy.Females with malignant tumor history or other severe diseases (e.g., liver failure, heart failure, etc.), whose life expectancy is less than 12 months.Females who (1) have historical HPV vaccination, or (2) are in non-exposed groups but have clear intention for HPV vaccination in next 3 years (confirmed by field investigators before enrollment).Any high-risk HPV (hr-HPV) DNA (i.e., HPV 16/18/*31/33/35/39/45/51/52/56/58/59/66/68*) positive result at baseline.Having abnormal colposcope diagnosis or cervical diseases at the baseline screening (women tested HPV positive or having abnormal colposcope diagnosis or cervical disease will be followed up and managed through the local referral system).

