### Endpoints

#### Primary endpoint

Cervical infection with HPV-16 and/or HPV-18 (by PCR), *defined as at least one positive HPV-16 or HPV-18 DNA PCR assay at enrollment (Month 0) or follow-up (Month 36) or any additional screenings during the study period.*

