### Data collection

All the data collected from the surveys and cervical cancer screenings will be documented in the YRHIP, (approval No.: GKYBSZ [2020] No. bc0015; Applicant: Ningbo Yinzhou Center for Disease Control and prevention; Approval time: October 2020).

Once the subject is recruited into the study with signed informed consent form, she will be identified in the YRHIP via her resident identification number and marked as the study subject, and new subpage which contains the study data will be created on her personal file in the YRHIP. The data of the paper-based questionnaire survey will be transcribed into corresponding fields and the cervical cancer screening data will be synchronized with existing healthcare activity page on real-time. Besides the survey and screening data, we’ll also obtain the data of general information, enrollment date, scheduled time of second visit, call-back status, HPV vaccination history, self-initiated cervical cancer screening, cervical related treatment or medication from the YRHIP.

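### Kaplan–Meier curves are planned for endpoints observed mainly at one scheduled Month 36 test, so their shape shows when women were tested, and their end-point can be inflated under one ordinary way of coding the dates

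*Protocol article*

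**What the plan says.** All references are to the protocol article; no separate SAP is shown.

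- **Statistical analysis** commits to a survival display: "the Kaplan–Meier method will be used to draw the survival graph, based on the actual number of cases of each endpoint". It names no event date, censoring date or time unit. The effect estimate comes from elsewhere: a logistic regression in each birth cohort, reported as one minus the relative risk.
- **Study procedure** states that "two visits will be scheduled for all subjects at Month 0 and Month 36", and that "the second screening with type-specific HPV DNA PCR testing will be given within 2 weeks after the call-back". It does not say how call-back dates are spread around Month 36.
- **Exclusion criteria** remove women with "Any high-risk HPV (hr-HPV) DNA" found at baseline, so an incident event can be found only after Month 0.
- **Primary endpoint** also counts a positive result at Month 36 "or any additional screenings during the study period", and **Data collection** takes "self-initiated cervical cancer screening" from the regional platform. No frequency is given. **Background** gives the local routine after a negative result: "those who are tested negative will be invited for another screening after 3 years".

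**The concern.** Kaplan–Meier needs an event time for each case and, at each such time, a risk set of women in whom the event could have been seen. Neither is available here. A woman found positive at Month 36 became infected at some unknown point in the preceding three years, and a woman can register an event only on a day when she is tested.

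Two consequences follow:

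1. **Shape.** With detection dates as event times, the curve is almost flat for three years and then drops. Any earlier steps show who happened to be screened early. A reader would take both as information on when infection occurs.
2. **Height.** During the Month 36 call-back, women who test negative may leave the risk set while untested women remain in it. Later positives are then divided by a shrinking denominator, and the curve can end well above the proportion infected.

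Describing incidence by exposure status is a stated aim, so a figure that misdescribes it matters even though no test is attached to it.

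**Working it through.** **Inputs**

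- True proportion positive by Month 36: p = 0.02 in the non-exposed group (Table 1). The table gives no time base; I take it as the three-year proportion. For the 31–45 cohort at 50% effectiveness, the exposed value is 0.02 × (1 − 0.50) = 0.01.
- Test window: 14 days from call-back (Study procedure). A 14-day spread in time since enrolment assumes that call-back falls at the same point for every woman. Spreads of 30, 60 and 90 days are my assumptions.
- Group sizes: 661, 1208 and 2371 per group (Table 1).

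**The plan's own figures.** The article states no Kaplan–Meier figure. Table 1 can be checked with n = [1.960·√(2p̄q̄) + 0.842·√(p₁q₁ + p₂q₂)]² / (p₁ − p₂)². For 0.02 against 0.01 this is (0.3369 + 0.1446)² / 0.0001, or 2319 after rounding up, against 2371 stated. The other cohorts give 658 (661 stated) and 1190 (1208 stated). All are within 3%, so 0.02 was used as a simple proportion, as here.

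**Formula.** Suppose n women are each tested once, evenly over k days, and negatives are censored on their test day. When j days of testing remain, n·j/k women are at risk and n·p/k test positive, so the hazard is p/j. The curve ends at

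1 − (1 − p/1)(1 − p/2)…(1 − p/k), which is roughly p × (1 + 1/2 + … + 1/k).

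With k = 2 and p = 0.02: 1 − 0.98 × 0.99 = 2.98%, already 1.49 times the truth.

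| Spread (days) | End-point at p = 0.02 | Ratio | End-point at p = 0.01 | Ratio |
|---|---|---|---|---|
| 1 | 2.00% | 1.00 | 1.00% | 1.00 |
| 14 | 6.33% | 3.16 | 3.21% | 3.21 |
| 30 | 7.71% | 3.85 | 3.92% | 3.92 |
| 60 | 8.97% | 4.48 | 4.58% | 4.58 |
| 90 | 9.70% | 4.85 | 4.96% | 4.96 |

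Simulation with exponential infection times (2371 women, 300 runs) gave mean ratios of 3.2, 3.9 and 5.1 for even spreads of 14, 30 and 90 days. Uneven spreads (normal or exponential test dates, all three group sizes) gave median ratios of 3.8 to 5.7 and means of 6.0 to 8.2.

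**Other codings, same data (simulation, 1208 women, except the tied case)**

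- Negatives censored at one common closing date: 1.0 (14 or 90 days).
- All tests coded as the scheduled Month 36 visit: 1.0, because the curve is then a single step of height p.
- Time in months: 1.0 for a 14-day spread, 1.9 for 90 days.

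**Interim tests (day-level dates, negatives censored on the test day).** If 10%, 30%, 50% or 100% of women have one interim test, the ratio is 3.1, 2.9, 2.7 or 2.1 for a 14-day spread, and 4.9, 4.5, 3.9 or 3.1 for 90 days.

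**Between groups (same day-level coding).** With equal spread in both groups (14 to 90 days), effectiveness read from the curves barely moves: 83% becomes 82.3–82.6%, 66% becomes 64.9–65.4%, and 50% becomes 48.8–49.3%. With unequal spread, a true 50% reads as 1 − 3.207/9.695 = 66.9% (exposed 14 days, non-exposed 90) or 1 − 4.963/6.326 = 21.5% (the reverse).

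**The case against.** The strongest reply is that the article fixes no event date, censoring rule or time unit. These are commonly left to a fuller document, and several ordinary choices give no inflation. That stands. A reader might infer that the curve will overstate infection three- to five-fold as a matter of fact. The documents do not support this: the figure needs day-level dates, negatives censored on their own test day and a given spread of tests. Only the two-week window is documented, and the upper part of the range rests on assumed spreads.

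Two further points limit the size. Additional and self-initiated screenings count and lower the ratio, although their frequency is unknown and the three-year routine interval suggests that it may be low. Much of the inflation also sits in the last, small risk sets. Dropping the final day of 14 leaves 3.25 − 1 = 2.25 in the harmonic sum, and dropping the last 9 of 90 days leaves 5.08 − 2.83 = 2.25. A curve cut off there is inflated about 2.25-fold whichever spread applies.

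A reader might also infer that the curves would contradict the logistic result or bias the effectiveness estimate. The documents do not support that either. The curve is a display only, with no log-rank test or hazard ratio planned, and nothing indicates that call-back will differ between groups.

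None of this rescues the timing. A later document can define dates, but it cannot recover infection times that were never observed. The codings without inflation either collapse the curve to the crude proportion or treat women as known negatives after their last test.

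**Conclusion.** The point holds as a fault in a stated descriptive method. With one scheduled test after baseline, infection time is interval-censored over about 36 months, and the shape of a Kaplan–Meier curve reflects the testing calendar under any coding of the dates. That part needs only the visit schedule, the baseline exclusion and the premise that unscheduled screening is not frequent.

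The inflated end-point is conditional. At a true 2.0%, with day-level dates and censoring on the test day, the curve ends near 6.3% for tests spread evenly over 14 days and near 9.7% for an assumed 90 days. Other ordinary codings give 1.0 to 1.9 times the truth. The calculation covers HPV positivity only. For lesions, the timing argument carries over because the study visits find them through the same HPV-first screening, but I have not sized the inflation.

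The logistic estimate of effectiveness and the sample size do not depend on the curve.

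**What to change.** Replace the Kaplan–Meier sentence with, for example:

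*For each endpoint, the cumulative proportion of women with the event detected by the Month 36 visit will be reported with an exact 95% CI, by exposure group and age cohort.*

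For the endpoint of infection lasting over 12 months, take the proportion after its own confirmatory test.

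If a curve is wanted, use the interval-censored non-parametric (Turnbull) estimate. The last negative and first positive tests are the interval ends, and women never positive are right-censored at their last negative test. State a rule for women not screened at Month 0 (for example, before sexual debut), who have no negative test to start from.

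The cost is one sentence. Incidence by age cohort and exposure status is already planned, with categorical data as proportions, so only the exact interval is new. The downside is that no conventional survival curve is shown.

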### Sample size

Per the previous research, the effectiveness assumptions for *Cervarix* will be 83%, 66%, and 50% for the cohorts of 9–20, 21–30 and 31–45 years of age respectively [23, 24]. The frequency of exposed group vs. non-exposed group will equal to 1: 1 with the level of significance α = 0.05 and statistic power 1-β = 0.8. The statistical analysis was performed on PASS15.0 (Tests for Two Proportions). Considering the loss to follow-up (5% estimated) and subtraction due to the baseline HPV infection and the contamination during follow-up (25% estimated), there will be 30% loss at the end of study. To mitigate this, the targeting recruitment number will be 1/(1–0.3)*100% of the sample size of effectiveness calculation. The detailed variables and calculation of the sample size is demonstrated in the table below (Table 1).

**Table 1 Tab1:** Sample size calculation

Age group(y/o)	Incidence of HPV 16/18 infection	Vaccine effectiveness	Frequency ratio	Exposure group	Non-exposure group	Sample size for effectiveness calculation	Targeting recruitment number
9–20	0.02	0.83	1:1	661	661	1322	1890
21–30	0.02	0.66	1:1	1208	1208	2416	3452
31–45	0.02	0.50	1:1	2371	2371	4742	6776
Total	-	-	-	4240	4240	8480	12,118

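### The per-cohort adjusted logistic model with vaccine interactions is too rich for the 9–20 cohort, where Table 1 implies about 15 HPV 16/18 events, about 2 of them in vaccinated women

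*Protocol article*

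**What the plan says.** The Statistical analysis section of the protocol article fixes four things.

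- **Model and level of fitting:** "The Logistic Regression will be performed to analyze the impact on HPV 16/18 infection, and HPV 31/33/45 infection in each birth cohort", three years after vaccination.
- **Adjustment:** demographic characteristics, sexual history and personal behaviour are given as examples. The list is left open and the number of terms is not stated.
- **Effect modification:** six factors are listed (frequency of sexual activity, number of partners, extramarital sexual activity, family income, education, screening history). Then: "The interaction term between the above factors and HPV vaccination will be introduced into the Logistic regression model". Models with and without the term are compared.
- **Reported quantity:** "The vaccine impact will be calculated by using (1-Relative Risk) and its 95% CI".

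The Sample size section plans each age cohort separately with an unadjusted comparison: "The statistical analysis was performed on PASS15.0 (Tests for Two Proportions"). It states that "the effectiveness assumptions for *Cervarix* will be 83%, 66%, and 50% for the cohorts of 9–20, 21–30 and 31–45 years of age", and Table 1 sets the unvaccinated incidence at 0.02 in every cohort.

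The Study procedure section adds that effectiveness will be assessed as an exploratory objective if numbers suffice. It gives no threshold and no alternative model. The Aims section, however, places effectiveness against HPV 16/18 within the first objective.

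**The concern.** Table 1 sizes each cohort just large enough for a crude two-proportion test. The planned analysis asks much more of the same data: several adjustment terms, and then vaccine-by-factor interactions. What a logistic model can support depends on the number of events, not of participants, and the scarcer outcome category here is very small in the youngest cohort.

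The difficulty is greatest when the vaccine works best. If no vaccinated girl or woman aged 9–20 is infected, or if none is infected at some level of a factor, standard maximum likelihood gives a vaccine or interaction coefficient that runs off to infinity. The cohort with the highest assumed effectiveness could then be the one without a usable adjusted estimate or Wald interval.

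**Working it through.** **Inputs (Sample size section and Table 1).** Unvaccinated incidence p1 = 0.02. Effectiveness VE = 0.83, 0.66, 0.50. Per group n = 661, 1208, 2371. The design is stated "with the level of significance α = 0.05 and statistic power 1-β = 0.8".

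**Step 1: reproduce the plan's figure.** With p2 = 0.02 × (1 − VE), a two-sided pooled two-proportion formula without continuity correction gives 658, 1190 and 2319 per group. Table 1 has 661, 1208 and 2371, so the differences are 0.5%, 1.5% and 2.2%. Power at the stated n is 0.802, 0.806 and 0.809. Table 1 is reproduced, and it uses 0.02 directly as the proportion infected.

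**Step 2: expected HPV 16/18 events**, n × p1 and n × p2:

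| Cohort | Unvaccinated | Vaccinated | Total |
|---|---|---|---|
| 9–20 | 661 × 0.02 = 13.2 | 661 × 0.0034 = 2.2 | 15.5 |
| 21–30 | 1208 × 0.02 = 24.2 | 1208 × 0.0068 = 8.2 | 32.4 |
| 31–45 | 2371 × 0.02 = 47.4 | 2371 × 0.01 = 23.7 | 71.1 |

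Even if all 1890 recruits aged 9–20 were analysed (945 per group), there would be 18.9 + 3.2 = 22.1 events.

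**Step 3: events per parameter.** The number of parameters is not stated, so a range is assumed.

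| Cohort | 5 parameters | 10 parameters | 15 parameters |
|---|---|---|---|
| 9–20 | 3.1 | 1.5 | 1.0 |
| 21–30 | 6.5 | 3.2 | 2.2 |
| 31–45 | 14.2 | 7.1 | 4.7 |

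**Step 4: chance of no vaccinated case.** P(0) = (1 − p2)^n.

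- 9–20: 0.9966^661 = 0.105.
- 21–30: 0.9932^1208 = 0.0003.
- 31–45: negligible.

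Only participants who have had sexual debut and are willing are screened (Study procedure), so the number tested at 9–20 may fall below 661 per group. The article gives no fraction. If half were tested (an assumption), P(0) = 0.9966^330 = 0.325.

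**Step 5: interactions at 9–20 with the full 661 per group.** Take one binary factor split 50/50 (an assumption). Each level expects 2.247 / 2 = 1.124 vaccinated events.

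P(at least one level has none) = 1 − (1 − e^−1.124)² = 0.54.

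The same formula for 21–30 uses 8.21 / 2 = 4.11 and gives 1 − (1 − e^−4.11)² = 0.03.

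For six independent 50/50 factors at 9–20, let K be the number of vaccinated events. A factor has an empty level with probability 1 if K is 0 or 1, and 2^(1−K) otherwise. Averaging 1 − (1 − 2^(1−K))^6 over the binomial distribution of K gives about 0.85 that at least one of the six interactions is not estimable. Less balanced factors make this worse.

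**Step 6: odds ratio against relative risk.** OR = [p2/(1 − p2)] / [p1/(1 − p1)]. At p1 = 0.02, 1 − OR is 83.3%, 66.5% and 50.5%, against 1 − RR of 83%, 66% and 50%. The gap is 0.3 to 0.5 percentage points.

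**The case against.** Several points on the other side have force.

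- **The estimator is not named.** The article says only logistic regression. A reader might infer that plain maximum likelihood with Wald intervals and a long covariate list has been fixed. The text does not say so, and a fuller document could name penalised or exact estimation. This stands as a limit on the wording. It does not remove the mismatch between the event count and a per-cohort adjusted model with interactions, both of which the article does fix.
- **The analysis would not be uncomputable.** A reader might infer that the effect could not be estimated at all. That goes too far. With no vaccinated case, a profile-likelihood or exact bound still exists. A likelihood comparison of models with and without an interaction can still be computed, though it is weak. The crude incidences and chi-squared tests do not depend on the model.
- **Interactions may be meant for pooled data.** The interaction sentence does not repeat the per-cohort phrase, and the Strengths section speaks of adjusting for age in multi-factor analysis. Per-cohort testing is the natural reading, because the sentence refers back to the logistic model just defined. It is not the only reading.
- **Effectiveness is called conditional and exploratory.** This mitigates only in part, because the Aims section and Table 1 are built on effectiveness in every cohort.
- **The 0.02 has no time unit.** If it were annual (an assumption), three-year incidence would be 1 − 0.98³ = 0.0588. The 9–20 cohort would then expect about 45 events (6.6 vaccinated), and P(0) would fall to about 0.1%. Table 1, however, uses 0.02 as the proportion itself.
- **The odds-ratio point is small.** A reader might infer that reported effectiveness would be materially distorted. At 2% incidence it would not.

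**Conclusion.** The point holds as a cheap improvement. On Table 1's inputs the 9–20 cohort cannot support the adjusted logistic model with interactions that the article describes: 15.5 expected events, 2.2 of them vaccinated; a 10.5% chance of a non-finite maximum-likelihood vaccine coefficient; and a 54% chance that a single 50/50 factor has a level without a vaccinated event. The problem is severe at 9–20, moderate at 21–30 and mild for main effects at 31–45.

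The event counts and the 10.5% rest only on the article's figures, with 0.02 read as the three-year proportion. The 54% also assumes a balanced binary factor. The 33% assumes that half are tested. The events per parameter depend on a covariate count that the article does not give. The step from odds ratio to relative risk is a minor matter of consistency.

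**What to change.** Amend the Statistical analysis section in three places.

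1. **Cohort-specific vaccine effect.** Use Firth-penalised logistic regression with profile-likelihood intervals, at least at 9–20. Adjust through one propensity score (exposure is planned 1:1, so it can be estimated well) or a small pre-specified covariate set.
2. **Interactions.** State that they are tested only in the pooled 9–45 sample, with age cohort as a stratum.
3. **Effect measure (minor).** Either report 1 − OR, labelled as approximating 1 − RR, with a gap of at most about 0.5 points at 2% incidence; or obtain the RR by standardising predicted risks and state its interval method, such as the bootstrap. If the risks come from a Firth fit, use the intercept-corrected form. With a single binary exposure, plain Firth gives a predicted risk of (x + 0.5)/(n + 1) for x events among n, which is biased upward when events are rare, and the bias would pass into the RR.

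**Cost.** Wording and slightly more programming; no extra participants or data. Firth also shrinks the estimate slightly. In an unadjusted example with 2 of 661 vaccinated and 13 of 661 unvaccinated infected, maximum likelihood gives 1 − (2/659)/(13/648) = 84.9%, and Firth gives 1 − (2.5/659.5)/(13.5/648.5) = 81.8%. With 0 and 13 cases, maximum likelihood has no finite coefficient, whereas Firth gives 1 − (0.5/661.5)/(13.5/648.5) = 96.4%.
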